### 2.6. Internet-Based Study Equipment

The specifications of the internet platform which has been designed included (1) compliance with international guidelines on clinical research and data security, (2) fast and reliable uploading of clinical data and SDF/OPS images, and (3) facilitating adequate two-way communication. To facilitate communication, an e-mail server and an open access website (http://www.microcirculationstudies.org) have been developed. The website provided general study information and included a weblog and a frequently asked questions section to keep participants updated on the latest study news. For data exchange, a dedicated database has been developed, based on Open Clinica (OC) 3.1 open source (GNU LPGL license) clinical trial software [37]. OC is, amongst others, in compliance with 21 CFR Part 11 (FDA), ICH-GCP and the US Health Insurance Portability and Accountability Act of 1996 (HIPAA). It is a Java J2EE-based application that runs on both Linux and Windows servers. Several other large multicenter studies have used OC databases, for example, the European Surgical Outcomes Study (EuSOS) and the Fluid Expansion As a Supportive Therapy (FEAST) trial [38, 39]. OC allows customization of its database to meet study requirements. The electronic CRF is defined using a special Excel sheet, which is uploaded to the server to define the CRF in the database. For the OC database, a dedicated server is available. Every participating center can log in to a part of the database that is assigned to their ICU to fill out the electronic CRF. After completion of data collection, data will be exported to SPSS 18.0, IBM, New York, USA, for statistical analysis.

A USB stick has been provided to each center with software developed specifically for this study. Its purpose is to provide the user a film editor so that captured film fragments can be edited to identify suitable clips for submission to the study center in Leeuwarden and to provide the needed communication protocols with the servers. The raw SDF/OPS image file can be imported in the image-editing program. By playing the SDF/OPS video, the user will be able to set a start mark and end mark at the appropriate points of the SDF/OPS clip, defining the part of the raw SDF/OPS file that will be used for subsequent analysis. The limit for the maximum clip length is set at 500 frames, that is, 20 seconds. In that way, we will be able to look for the part of the clip that is most suitable for analysis. The software on the USB stick automatically establishes an Internet connection with the central dedicated microSOAP study server using the required communication protocol and security settings. Backup copies of the clips are automatically stored on the USB stick. In case of failure of Internet connection, the USB stick containing the backup clips can alternatively be sent to the study coordinator by regular mail.

### 2.7. Data Analysis

#### 2.7.1. Sample Size Calculation

Because this is the first extensive prevalence study on microcirculatory alterations ever done, with a primarily explorative character, a concise power calculation is virtually impossible. Based on previous studies, with a sample size between 25 and 50 patients, in heart failure, high-risk noncardiac surgery, sepsis, and paediatric ICU patients, significant correlations between the existence of microcirculatory alterations and parameters of morbidity and mortality could be established [6, 10, 12]. However, it is reasonable to assume that morbidity and mortality may be lower in a general ICU population. Therefore, we aim for a sample size ten times larger than previously reported in single-center subgroup studies. Since this is by far the largest cohort of in vivo microcirculatory research in humans ever done, practical limitations with respect to availability of SDF/OPS technique and skilled operators will undoubtedly play a significant role in the definitive sample size.

#### 2.7.2. SDF/OPS Image Analysis

The SDF/OPS image analysis will be performed by the researchers appointed by the initiators of this study in accordance with internationally accepted guidelines using dedicated software [34, 35]. The analysis will be conducted blinded to the origin of the film clips. In a suitable subgroup, an automatic assessment method will be performed as described elsewhere to investigate the suitability of such an automatic software for evaluation and quantification of microcirculatory alterations [40].

Due to the demanding imaging technique, quality of SDF images may vary between centers [41]. However, up-to-date externally validated image quality scoring systems appear to be lacking. To ensure consistency in SDF analysis, SDF analysis will be performed by researchers appointed by the principal investigators, taking care for ongoing feedback and aiming for consensus. Since several reports from different research groups have reported excellent inter- and intraobserver agreement for the SDF image analysis, the steering committee decided beforehand that this would not be an extra topic of this study [5, 10, 34].

#### 2.7.3. Statistical Analysis

Descriptive statistics will be used to describe the study population. Further statistical analysis will be conducted to relate the microcirculatory alterations to the severity of disease and other parameters. The primary outcome measure is the prevalence of microcirculatory alterations. There is no consensus about the thresholds for a “normal” and an “abnormal” microcirculation. Several researchers have reported on values of several microcirculatory variables in healthy volunteers; MFI of capillaries (<20 *μ*m) is reported to be 3.0 [2.9–3.0] (median [IQR]), 2.82 (0.1), and 2.97 (0.03) (mean(SD)) (IQR = interquartile range, SD = standard deviation) [5, 11, 42]. Therefore, one expects 95% of healthy subjects to have a small vessel MFI between 2.62 and 3 [11]. In healthy volunteers, PPVs (small vessels) well above 90% are described, whereas in septic patients, a capillary PPV of 78% (23%) is described [11, 42, 43]. In septic shock, norepinephrine dose >0.1 microgram/kg/min and a lactate >2 mmol/L were associated with a significantly lower PVD (12 [8–15] versus 14 [11–17] n/mm^2^ for norepinephrine dose >0.1 microgram/kg/min and 10 [8–13] versus 14 [11–17] n/mm^2^ for lactate >2 mmol/L), as well as a significantly lower PPV (80 [70–91] versus 100 [90–100]% for norepinephrine dose >0.1 microgram/kg/min and 82 [71–99] versus 93 [84–100]% for lactate >2 mmol/L) [44]. In uncomplicated major abdominal surgery, preoperative PPV (small vessels) was 89% (83–95) versus 79% (73–92) in patients who developed complications postoperatively [4]. In this study, ROC curves will be used to find cut off values of microcirculatory variables in relation to morbidity and mortality.

Secondary outcome parameters are the correlation between microcirculatory changes and macrohaemodynamic variables, correlations between microcirculatory changes, and length of ICU/hospital stay, mortality, and SOFA/APACHE II scores [45, 46]. Differences between several subgroups will be assessed using a *t*-test in case of normally distributed variables; in case of non-normally distributed variables, a nonparametric test will be chosen. Whenever applicable, forward stepwise logistic regression analysis will be used to test for associations between the severity of microcirculatory dysfunction and illness severity, mortality, and length of stay. In addition, the relation between microcirculatory alterations, applied therapy (e.g., fluid therapy and vasopressor therapy), and indicators of peripheral perfusion (e.g., lactate) will be explored. Furthermore, the geographical distribution of microcirculatory alterations will be assessed.

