## 3. Discussion

This study will be by far the largest cohort of in vivo microcirculation research. We aim to provide insight in the worldwide prevalence and distribution of microcirculatory alterations. The questions we hope to answer are the following:

Does the presence of microcirculatory alterations indicate impending bad outcome in terms of morbidity and mortality?Does the presence of microcirculatory alterations provide a more sensitive indicator of morbidity and mortality then conventional hemodynamic and oxygen derived parameters? Is the presence of microcirculatory alterations related to applied therapy, such as fluid therapy and vasopressors?Is there a difference between microcirculatory alterations in different patient (sub-) groups, and how are these geographically distributed, as well as over time?

We expect that the results of our study will make clinicians more aware of the presence and importance of microcirculatory alterations in daily practice, thereby leading to better identification of patients who are at risk of an unfavorable outcome. Furthermore, we hope to trigger researchers to develop methods enabling easier bedside evaluation of the microcirculation for detection of those at risk of “microcirculatory failure”, as well as interventions aimed at ameliorating the microcirculation. Hopefully, by putting the microcirculation in a central position in future ICU practice, outcome of critically ill patients will be improved.

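### The primary prevalence has no adopted variable or threshold, and the only cut-off method stated is tuned to the cohort's own outcomes

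*Protocol article*

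**What the plan says.** All the relevant text on the threshold is in one paragraph of section 2.7.3 of the protocol article.

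- It names the endpoint: "The primary outcome measure is the prevalence of microcirculatory alterations".
- It concedes the difficulty: "There is no consensus about the thresholds for a “normal” and an “abnormal” microcirculation".
- It summarises small-vessel MFI in three healthy samples: a median of 3.0 with IQR 2.9-3.0, a mean (SD) of 2.82 (0.1), and a mean (SD) of 2.97 (0.03). From one of these it concludes that "one expects 95% of healthy subjects to have a small vessel MFI between 2.62 and 3". It does not say that a value below 2.62 will count as abnormal.
- It lists PPV and PVD values from volunteers, septic patients and surgical patients, again without choosing a limit.
- It ends: "In this study, ROC curves will be used to find cut off values of microcirculatory variables in relation to morbidity and mortality".

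The secondary outcomes come in the next paragraph. They relate microcirculatory changes, and the severity of dysfunction, to mortality, length of stay and severity scores. The Discussion (section 3) puts the first study question in terms of presence or absence: "Does the presence of microcirculatory alterations indicate impending bad outcome in terms of morbidity and mortality". Section 2.5 says that mortality and length of stay are collected after the imaging session.

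**The concern.** A prevalence is a count of patients on the wrong side of a line, so the line must be drawn without reference to what later happened to those patients. An ROC-optimal cut-off answers another question: which value best separates good from bad outcomes in this sample. It moves with the particular deaths observed. The sentence also speaks of variables in the plural and of both morbidity and mortality, so several cut-offs could result.

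Two things are at stake. First, the headline figure could be a by-product of the outcome data, and so not comparable with other cohorts. Second, if the same cut-off is then used to ask whether presence of alterations predicts death in the same patients, the search for the best cut-off inflates the apparent answer. The article mentions no split sample, bootstrap or external validation.

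**Working it through.** **1. The plan's own figure.** Mean minus 2 SD in the healthy sample with mean 2.82 and SD 0.1 is 2.82 − 2 × 0.1 = 2.62, which reproduces the stated limit (1.96 SD gives 2.624). The upper end, 2.82 + 0.2 = 3.02, exceeds the maximum score and is capped at 3. The same rule in the other healthy sample gives 2.97 − 2 × 0.03 = 2.91. The article's own sources therefore support at least two different limits.

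**2. Inputs for the simulation.** From the article: about 500 patients; MFI scored up to 3 in four quadrants and averaged. Assumed, because the article does not give them: mortality of 15-25% (75-125 deaths); MFI equal to 3 minus an exponential deficit with mean 0.25, rounded to steps of 1/12; the Youden index as the ROC criterion; a chi-square test of the dichotomised variable against death. The moderate association gives non-survivors a mean deficit 1.5 times larger, which before rounding is an AUC of 1.5 / (1 + 1.5) = 0.60.

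**3. Prevalence with a threshold fixed in advance (no association).**
- MFI below 2.62 means a score of 31/12 = 2.583 or lower, that is an unrounded deficit above 4.5/12 = 0.375. Prevalence = exp(−0.375/0.25) = exp(−1.5) = 22.3%.
- The 95% half-width is 1.96 × √(0.223 × 0.777 / 500) = 3.6 points.
- MFI below 2.91 means a score of 34/12 = 2.833 or lower, an unrounded deficit above 1.5/12 = 0.125. Prevalence = exp(−0.5) = 60.7%.

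**4. Prevalence and test with the ROC cut-off.**

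| Quantity | No association | Moderate association |
|---|---|---|
| Prevalence, 5th-95th percentile | about 0.5-85% | about 10-63% |
| Youden index, apparent | 0.04-0.05 | about 0.17 |
| Youden index, true at that cut-off | 0 | about 0.13 |
| p < 0.05 in the same patients | 13-15% | not a false-positive rate |

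With a cut-off fixed in advance, the false-positive rate stays at about 5%.

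**5. Dependence on the model.** A second simulation used a normally distributed marker, mortality of 10-30% and the same Youden rule. With no association, the 95% range of the prevalence was about 2-98% and 24-25% of tests were significant, against 4-5% with a fixed cut-off. With non-survivors shifted by 0.3 SD, the prevalence ranged over about 12-80%. The direction was the same in every setting; the size was not.

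**The case against.** The strongest reply is that the article never says the ROC cut-off will define the primary prevalence. A reader might infer a commitment to do so, because the sentence closes the primary-outcome paragraph. It can equally be read as a prognostic analysis serving the questions in the Discussion. This stands, and the point about prevalence is therefore conditional. It does not remove the problem: on the milder reading the primary outcome has no adopted variable or threshold, and the only method offered for finding one is outcome-driven.

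A second reply is that a condensed article leaves details to the full protocol or analysis plan. That is fair for the choice of ROC outcomes and for internal validation. It does not cover a method the article states.

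Third, a reader might infer that every later association result will be optimistic. The text does not support this. Section 2.7.3 plans correlations with microcirculatory changes and regressions on severity, which can use continuous MFI, PPV or PVD and are then untouched by any cut-off. The optimism is confined to dichotomised analyses.

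Fourth, the widest range assumes that MFI is unrelated to death, whereas the Introduction and section 2.7.1 report associations in earlier studies. This stands: the moderate-association range is the more relevant one, and it is still very wide.

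Finally, the study calls itself primarily explorative. That explains the missing power calculation, but a primary outcome still needs a definition.

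**Conclusion.** The concern holds in conditional form. The primary outcome has no adopted definition of abnormal, and the one stated route to a cut-off uses morbidity and mortality in the same patients. If that route defines the prevalence, the estimate could fall almost anywhere from 10% to 63% under a moderate association, against a sampling error of about 4 points either way for a threshold fixed in advance. If the same cut-off is used for the presence-of-alterations questions, apparent sensitivity and Youden index are too high and p-values too small.

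These sizes rest on the assumed mortality, MFI distribution and Youden rule; only the direction is robust. Nor do the documents show that 2.62 is the correct limit, tempting as it is to read it so. It is one of two limits obtainable from the quoted samples, it applies a normal-theory range to a capped score, and in the assumed model moving to 2.91 takes the prevalence from about 22% to about 61%. The gain from fixing a threshold is that the choice no longer depends on the outcome data, not that the choice is beyond dispute.

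**What to change.** Before outcome data are linked to the image scores, amend section 2.7.3 as follows.

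- State one primary variable and one threshold taken from healthy-volunteer data, not from ROC curves. Small-vessel MFI below 2.62, already cited there, is one candidate.
- Report the prevalence with a 95% confidence interval, and beside it the prevalence at other healthy limits, for example MFI below 2.91 and PPV below 90%.
- State that ROC cut-offs are exploratory and do not define the primary prevalence. Correct their performance for optimism with a bootstrap that repeats the cut-off search in each resample.
- Base the association with mortality on the continuous variable.

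The cost is wording and some extra computation; no new data are needed. The downside is real: any healthy limit is open to debate and the prevalence is sensitive to it, so the sensitivity thresholds must appear next to the primary figure.

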## 1. Introduction

The microcirculation plays a pivotal role in oxygen delivery to the tissue [1]. It is believed to be a key player in several disease states, such as sepsis and shock. The development of Orthogonal Polarizing Spectral (OPS) imaging and more recently Sidestream Dark Field (SDF) imaging has enabled bedside imaging of the—predominantly sublingual—microcirculation [2, 3]. Main advantage of SDF/OPS imaging is the ability to visualize true capillary hemodynamics in a noninvasive way at the bedside, thereby providing functional information related to the microcirculation where oxygen delivery to the parenchymal cells takes place. With SDF/OPS imaging, the presence of microcirculatory alterations in different critical care patient subgroups, such as sepsis, heart failure, and major surgery, has been widely explored during the past decade [4–9]. These microcirculatory alterations appear to be associated with an adverse prognosis; they are more severe in nonsurvivors in comparison to survivors in sepsis and heart failure, and are associated with the development of complications in abdominal surgery [4–12]. The aforementioned studies have all shown that microcirculatory alterations are apparent in the presence of more or less normal systemic haemodynamic parameters, thereby stressing the potential importance of the microcirculation as an additional target for resuscitation. Several interventions, ranging from vasoactive drugs and fluid therapy to circulatory assist devices, have been shown to have varying effects on their capacity to influence microcirculatory failure [7, 13–22]. 

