
ICU's were selected based on SDF/OPS availability, established skills in OPS/SDF imaging as demonstrated in a separate teaching course, and/or publications in this field. For image quality check, centers were asked to provide a representative SDF/OPS video of a septic patient and a healthy volunteer, enabling feedback on image quality. During an investigators meeting in March 2011, the study was scheduled for the second week of September 2011. For logistic reasons, it was decided that centers could choose two or more consecutive days for performing measurements. To prevent overlap of patient inclusion, ICU's were divided into (virtual) units and measured as one unit per day. A medical steering committee was formed to oversee the study, including representatives from the different continents as well as the major centers in the participating countries. The medical steering consisted of, [name], MD, PhD; [name], MD; [name]; [name], MD; [name], MD, PhD; [name], MD, PhD; [name], MD, MPH; [name], MD, PhD; [name], PhD. The study is coordinated from Medical Center Leeuwarden by the principal investigator ([name], MD, PhD), a dedicated physician in charge of running the communication ([name], MD) and a research nurse ([name]). The study center ensures communication with and between study centers, coordinates study logistics, and manages data analysis.

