### 2.2. Patient Selection

Every ICU patient ≥18 years, regardless of the underlying disease, was eligible for inclusion. Informed consent was obtained in accordance with local ethics approval. Participation in another study was no exclusion criterion, except when contradictory to local regulations. Patients <18 years or without informed consent were excluded, as well as patients with mucosal bleeding/injury or recent maxillofacial surgery that interfered with SDF/OPS imaging.

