### 2.5. Data Collection

The sublingual microcirculation was measured once in every patient. In line with internationally accepted consensus, 3 to 5 stable sublingual microcirculatory image sequences of 10–20 seconds were obtained for every patient [34, 35]. Along with the SDF/OPS imaging, data on demographics, reason for ICU admission, illness severity scores, haemodynamics, laboratory values, and treatment were collected. Afterwards, information on ICU/hospital length of stay and ICU/hospital mortality will be collected.

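### Correlating one measurement from an arbitrary ICU day with length of stay mixes time already spent and death with outcome, so size and sign cannot be read as prognosis

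*Protocol article*

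**What the plan says.** Section 2.5 (Data Collection) states: "The sublingual microcirculation was measured once in every patient". The timing follows the calendar. The Methods paragraph on selecting and scheduling centers fixes a study week and says "centers could choose two or more consecutive days for performing measurements". Section 2.2 sets no limit on days since admission: "Every ICU patient ≥18 years, regardless of the underlying disease, was eligible for inclusion". The result is a prevalent sample, imaged at whatever point of the stay each patient had reached.

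On follow-up, section 2.5 says: "Afterwards, information on ICU/hospital length of stay and ICU/hospital mortality will be collected". Section 2.7.3 (Statistical Analysis) then names as secondary outcomes "correlations between microcirculatory changes, and length of ICU/hospital stay, mortality, and SOFA/APACHE II scores", and adds forward stepwise logistic regression, where applicable, for "associations between the severity of microcirculatory dysfunction and illness severity, mortality, and length of stay". The article does not say when the count of stay begins or how patients who die enter a length-of-stay analysis.

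The Introduction says of microcirculatory alterations that "they are more severe in nonsurvivors in comparison to survivors in sepsis and heart failure".

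**The concern.** Two separate problems arise if the analysis is carried out as described.

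- **Time before the measurement.** A one-day sample catches long stays more often than short ones, and part of each stay has already passed when the camera is applied. A measurement cannot predict days that precede it. If the microcirculation changes over an ICU stay, or is related to how long the patient has been there, those past days can produce a correlation by themselves.
- **Death.** A patient who dies soon after imaging has a short stay. If alterations go with death, as the article's own Introduction says, deaths push the correlation toward shorter stay with worse microcirculation. In the length-of-stay result, that looks like quicker recovery.

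At stake is the interpretation of a named secondary outcome in a study whose Conclusion hopes to guide the design of a goal-directed interventional study.

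**Working it through.** **The plan's own figure.** Section 2.7.1 cites studies of 25 to 50 patients and says "we aim for a sample size ten times larger than previously reported in single-center subgroup studies". Ten times 25 to 50 is 250 to 500, and the upper end agrees with the roughly 500 patients in the Conclusion. N = 500 is used below. The article gives no stay distribution, mortality rate, effect size or time from admission to imaging, so every other input here is an assumption.

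**1. Share of the stay already past.** Assume exponential ICU stays with mean 5 days. A patient found in the unit on a given day has elapsed time E and remaining time R, independent and each with mean 5. Mean total stay among those sampled is 5 + 5 = 10 days, and 5/10 = 50% precedes the measurement.

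**2. Dilution.** Let the marker be related to R only. Since Var(E + R) = 2 Var(R), its linear correlation with total stay is 1/√2 = 0.71 times that with R. A rank-correlation simulation gave 0.291 with remaining stay and 0.197 with total stay; 0.197/0.291 = 0.68, a loss of about 30%.

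**3. Correlation created by elapsed time.** Let the marker be related to E only, with no relation to R. The chance of p < 0.05 (two-sided) is Φ(atanh|r| × √497 − 1.96).

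| r with elapsed time | r with total stay (simulated) | atanh(r) × √497 | Significant at N = 500 |
|---|---|---|---|
| -0.05 | about -0.03 | 0.67 | about 10% |
| -0.10 | about -0.065 | 1.45 | about 31% |
| -0.20 | about -0.13 | 2.91 | about 83% |

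**4. Death.** With constant daily hazards of discharge d and ICU death h, mean stay is 1/(d + h) and the proportion dying is h/(d + h).

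| Group | d | h | Proportion dying | Mean stay, days |
|---|---|---|---|---|
| No alteration | 0.12 | 0.03 | 20% | 6.7 |
| Alteration, discharge unchanged | 0.12 | 0.08 | 40% | 5.0 |
| Alteration, slower discharge, still 40% dying | 0.09 | 0.06 | 40% | 6.7 |
| Alteration, slower discharge | 0.07 | 0.08 | 53% | 6.7 |
| Alteration, still slower discharge | 0.05 | 0.08 | 62% | 7.7 |

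With constant hazards, mean remaining stay from the measurement is also 1/(d + h). Moving the start of the count therefore does not remove the effect of death.

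**5. A second model.** This one assumes log-normal stays (survivor median 8 days, log-SD 0.9) and alterations in 20% at admission. The two-sided 5% critical |r| at N = 500 is 0.088.

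- Alterations affect neither death nor stay but resolve at 0.1 per day: r = -0.147 with total stay and -0.025 with remaining stay.
- Alterations resolve, lengthen survivors' stay 1.3 times and raise mortality from 15% to 45%, with median time to death 2 to 8 days: r = -0.119 to -0.141 with total stay in all patients, against +0.024 to +0.028 with remaining stay in survivors.
- Alterations persist and have no effect on survivors' stay, same mortality difference, median time to death 4 days: r with total stay = -0.050 in all patients and +0.009 in survivors.
- As the previous case, but survivors' stay 1.3 times longer: r with total stay falls from +0.105 in survivors to +0.038 in all patients.

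In these runs time before the measurement is the stronger mechanism. Death alone weakens the correlation or turns it slightly negative.

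**The case against.** The strongest reply is that the article does not define length of stay. A separate protocol went to the centers and is not shown, and it could count from the measurement and say how deaths are handled. This stands in part. The elapsed-time argument depends on the ordinary meaning of the term. The death argument does not, and neither a plain correlation nor logistic regression treats death as a competing event. The regression's candidate covariates are not listed, so adjustment for prior ICU days is neither planned nor excluded.

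A second reply is that the outcome is secondary in a study described as primarily explorative, that the Discussion's outcome questions name morbidity and mortality rather than length of stay, and that mortality is reported separately, so an excess of deaths would be visible beside a shorter stay. This is fair and limits the consequences. It does not make the length-of-stay result interpretable.

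A third reply is that the figures come from chosen inputs. This stands too. The false correlation fades as the link with elapsed time weakens, and the fall in mean stay disappears once discharge slows enough. The two models even assume opposite directions: a marker that worsens with time in the ICU in one (MFI falling), and alterations that resolve in the other.

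A reader might infer from all this that the planned correlation will have the wrong sign, or that alterations will appear beneficial. The documents do not support that: no input that would fix the sign is given. Nor does the half-of-stay figure carry over to hospital stay, because patients were sampled in the ICU and not evenly across their time in hospital.

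**Conclusion.** The concern holds in a limited form. As described, the analysis relates a single measurement on an arbitrary ICU day to a duration that, on its ordinary reading, began before the measurement and that death can end. The bias is structural, but its size and sign are unknown.

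Under the stated assumptions it ranges from negligible (about -0.03 from elapsed time, significant in about 10% of studies of 500) to material (about -0.13, about 83%). There is also about 30% dilution of any true correlation with remaining ICU stay, and a shift in mean stay from deaths that can be 1.7 days (6.7 - 5.0) or nothing. The result should not be read as prognostic. The primary prevalence outcome is unaffected. These calculations concern length of stay only and do not show a fault in the mortality analysis.

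**What to change.** Change the analysis wording for length of stay as follows:

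- Count ICU and hospital stay from the day of measurement.
- Analyse time to live discharge with death as a competing event, using a cause-specific or subdistribution model.
- Include ICU days before the measurement as a covariate in the length-of-stay model.
- Report any correlation with total stay as descriptive only.

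The cost is slightly more analysis work and the need for admission, measurement, discharge and death dates. Section 2.5 mentions durations and mortality rather than dates, so the sponsor should confirm that the dates are held or can be retrieved while outcome data are still being collected. No additional patients or imaging are required.
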